##### Patient and hospital information

demographics, comorbidities, prior year number of admissions for COPD, prior year use of NIV or IMV, and outcomes will be identified from ICD-10 procedure codes and billing codes. For each participating hospital, we will record the number of beds, the annual number of admissions for COPD, teaching status, geographic region, and whether it serves an urban or rural population. We will also collect information about staffing: number of RTs, hospitalists, emergency room physicians, and nurses. We will record if hospitals use protocols for NIV initiation and management, and if NIV can be delivered on the regular medical floor or only in an intensive care unit. These factors will be used to describe participant hospitals and evaluated as potential confounders or effect modifiers.

##### Noninvasive and invasive ventilation

For each patient, we will examine standardized charge codes generated daily by respiratory therapists as well as dated ICD-10-procedure codes to determine whether or not they were treated with assisted ventilation, and, if so, whether ventilation was NIV or IMV. We define the primary method of ventilation as the first method by date and distinguish between patients treated with NIV as an initial strategy from those in whom NIV use follow exposure to invasive mechanical ventilation (IMV). We have previously validated the NIV ICD procedure codes and respiratory therapy charge codes by retrospective medical chart review. Using ICD-9-CM codes alone yielded a sensitivity of 86% (95% CI, 81–92%) and specificity of 92% (95% CI, 84–98%). The approach of using ICD-9-CM procedure codes and/or respiratory therapist charges increased sensitivity to 99% (95% CI, 98–4 100%) without reducing specificity (92%, 95% CI, 84–99%) [31].

##### Statistical analysis of aim 1

We will generate descriptive statistics overall, by hospital and educational strategy, including counts and percentages for categorical data, means, standard deviations, and percentile distributions for continuous data. We will compare characteristics of hospitals, including staffing characteristics, in the two study arms via chi-square tests and *t* tests or Wilcoxon tests. Characteristics of patients in the enrolled hospitals in the two arms will be compared via GEE models accounting for clustering by hospital. We will calculate the percentage of patients treated according to each of the primary ventilatory strategies: no assisted ventilation, NIV, and IMV. We will then calculate the proportion of patients initially treated with NIV among those who received assisted ventilation. We will estimate a risk-standardized proportion of ventilated patients initially treated with NIV (RS-NIV) for each hospital and for each data collection period (baseline period, 18 months post-intervention, and between 18 to 36 months post-intervention). We will use hierarchical logistic regression with a random hospital effect to model initial use of NIV among patients started on ventilation, adjusting for demographics, and comorbidities. From the model, a predicted NIV percentage for each hospital will be computed as the NIV percentage that would be anticipated at a particular hospital by using its hospital random effect, given the patient case mix. The expected NIV percentage will be computed as the rate that would be expected if the same patient mix were treated at an “average” hospital, using the average hospital effect. The RS-NIV percentage is then computed as the ratio of predicted to expected NIV percentage standardized by the overall unadjusted mean NIV percentage for all admissions in our model. Risk standardization has 2 key advantages: it adjusts for differences in patient mix, which may impact the suitability of NIV; it also provides more stabilized estimates based upon Bayesian shrinkage towards the overall mean among hospitals with small numbers of ventilated patients [32, 33]. The mean and median RS-NIV rates of the two arms will be computed for each study period. The primary analysis will use an analysis of variance model to compare IPE to OLE on change in RS-NIV rates from baseline to 18 months post-intervention. Additional analyses will adjust for hospital characteristics that are unbalanced between the study arms. A secondary analysis will compare the post-intervention levels, adjusting for baseline RS-NIV. To assess sustainability, similar models will be used to compare level of RS-NIV after an additional 18 months have passed.

For the secondary outcomes, our analysis will calculate hospital RS-rates of NIV failure, mortality, 30-day readmission, and length of stay among ventilated patients, as well as all COPD admissions for each study period. We will compare outcomes of OLE and IPE hospitals using models described above. Although we assume that the patients treated in IPE hospitals will have better clinical outcomes, we do not expect it to be able to detect an effect of these strategies on secondary outcomes due to overall low outcome rate, the small projected change, and relatively small number of clusters.

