### Randomization

We will randomly allocate hospitals to one of the study arms, stratified by the baseline NIV proportion and hospital bed size. A researcher not involved in the study and blinded to the identity of the hospitals will use a computer-generated randomization scheme. The randomization scheme will be concealed to the investigators. Due to the character of the intervention, it will not be possible to blind participants or investigators providing the educational program; however, the investigators will not be aware of the results of the study by intervention arm until the analysis is finalized.

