The minimal number of hospitals participating in the trial was based on the analysis of Premier 2016–2017 data. Hospital RS-NIV proportions were calculated for the 457 hospitals with at least 35 eligible COPD admissions. The median RS-NIV rate among this group of hospitals was 82% (IQR 74–86%). We then selected the 48 hospitals with RS-NIV proportion less than 55%, based on the clinical impression that these hospitals would have sufficient room for improvement, as potentially eligible sites. Among these hospitals, the median number of eligible COPD patients was 197 over a 12-month period, ranging from 23 to 556 patients. The number of ventilated patients per hospital ranged from 7 to 163, with a median of 37. To achieve stability in estimation of hospital level RS-NIV, we will assess our primary endpoint at 18 months post-intervention expecting a minimum of 10 ventilated patients per hospital in which to assess NIV rates. Power analysis was conducted to determine the number of hospitals needed to assess the primary outcome of difference between the study arms in change in the hospital level risk-standardized proportion of ventilator starts that are NIV (RS-NIV). Using a type I error rate of 0.05, and standard deviation of change in rates over time derived from our prior work with the Premier data base, a total sample of 20 hospitals, 10 in each arm will give 80% power to detect difference of 15% in change (e.g., 5% increase among OLE hospitals, vs. 20% increase among IPE hospitals). Power is > 90% to detect a 20% difference in change between the intervention groups.

#### Aim 2

To examine the effect of OLE and IPE on RT autonomy and team functionality as potential mediators of NIV uptake.

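### The primary analysis is a change-score ANOVA and the baseline-adjusted comparison is only secondary; reversing the order and adding a bed-size term would gain power from data already held

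*Protocol article*

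**What the plan says.** Under Randomization, allocation of the 20 hospitals is "stratified by the baseline NIV proportion and hospital bed size".

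Under Statistical analysis of aim 1, the analyses are ranked. First: "The primary analysis will use an analysis of variance model to compare IPE to OLE on change in RS-NIV rates", with change taken from baseline to 18 months after the intervention. Then: "Additional analyses will adjust for hospital characteristics that are unbalanced between the study arms". Then: "A secondary analysis will compare the post-intervention levels, adjusting for baseline RS-NIV". Hospital characteristics are to be compared "in the two study arms via chi-square tests and *t* tests or Wilcoxon tests". The article gives no threshold for imbalance and no covariate list. No model is stated to contain bed size by design.

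Under Power and sample size for aim 1, the text reads "Using a type I error rate of 0.05" and then says that "a total sample of 20 hospitals, 10 in each arm will give 80% power to detect difference of 15% in change", with more than 90% power for a 20% difference. The SD of change is said to come from earlier work with the Premier database, but no value is printed.

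**The concern.** A change score enters the baseline with its coefficient fixed at 1. If the true slope of follow-up on baseline is lower, the excess baseline variation stays in the outcome as noise, and any chance baseline difference between arms is over-corrected. A slope below 1 is likely here. Hospitals are selected for a risk-adjusted NIV proportion below the median, and some have few ventilated patients: 7 to 163 per hospital over 12 months (median 37), with a minimum of 10 expected over 18 months.

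Stratified allocation also balances the arms on baseline NIV and bed size. If the analysis leaves those factors out, the variation they explain stays in the error term, so the standard error is too large for the design. With 20 hospitals, the trial has little precision to give away.

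A lesser issue concerns the additional analyses. Testing many hospital characteristics with 10 hospitals per arm, and adjusting for whichever appear unbalanced, leaves the adjusted result open to choice.

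**Working it through.** **Inputs.** From the article: 10 hospitals per arm, alpha 0.05 (two-sided assumed), 80% power at 15 points, more than 90% at 20 points. Not in the article, so assumed over a range: the SD of change, the correlation rho or slope b of follow-up on baseline, and the size of any bed-size effect.

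**1. The plan's own figure.** Without a printed SD, the 80% cannot be reproduced independently. Solving for the SD of change that gives 80% power at 15 points yields 11.3 points (noncentral t, 18 df) or 12.0 points (normal approximation). Either SD, with its own method, gives 96% power at 20 points, which agrees with the stated figure of more than 90%. I use 11.3.

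**2. Efficiency with equal SDs.** If both periods have SD s, Var(change) = 2s²(1 − rho) and the baseline-adjusted residual variance is s²(1 − rho²). The ratio is (1 + rho)/2. Residual SD = 11.32 × sqrt(ratio), with 17 df:

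| rho | variance ratio | residual SD | power at 15 points | difference detectable at 80% |
|---|---|---|---|---|
| change score | 1 | 11.3 | 80% | 15.0 |
| 0.3 | 0.65 | 9.1 | 93% | 12.1 |
| 0.5 | 0.75 | 9.8 | 90% | 13.0 |
| 0.7 | 0.85 | 10.4 | 86% | 13.9 |
| 0.9 | 0.95 | 11.0 | 82% | 14.7 |

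Spending one more df on bed size (16 df) costs about 0.2 to 0.3 percentage points of power.

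**3. Efficiency with restricted baseline spread.** Selecting low-NIV hospitals narrows the baseline distribution. Suppose, as an assumption, that it is the lower half of a normal, so that baseline variance is k = 0.363 of its unselected value. The residual variance is s²(1 − b²), and Var(change) adds (1 − b)²ks². The ratio is (1 + b)/[(1 + b) + k(1 − b)]:

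- b = 0.3: 1.3/(1.3 + 0.254) = 0.836, power 86%
- b = 0.5: 1.5/(1.5 + 0.182) = 0.892, power 84%
- b = 0.7: 1.7/(1.7 + 0.109) = 0.940, power 82%

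The detectable difference is then 13.8 to 14.6 points.

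**4. Leaving out the strata.** I simulated 20 hospitals randomised 10:10 within a two-by-two split of baseline and bed size (6,000 runs per setting, SD of change 11.3). Type I error at nominal 5%:

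| rho | change score, no bed-size effect | change score, assumed 10-point bed-size effect |
|---|---|---|
| 0.3 | 2.4% | 1.8% |
| 0.5 | 3.2% | 2.0% |
| 0.7 | 3.8% | 2.7% |

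Across all settings tried, the change-score range is about 1.5 to 4.9%. The model with baseline and bed size held 4.7 to 5.3% in the settings tabulated. With the 10-point bed-size effect, power for 15 points was 75 to 76% for the change score. For baseline plus bed size it was 92%, 89% and 85% at rho 0.3, 0.5 and 0.7. Adjusting for baseline alone, as the secondary analysis is worded, left type I error at about 3% in that setting, so the bed-size term matters if bed size predicts outcome.

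**The case against.** Both analyses are prespecified, and the change score matches the declared primary outcome and the basis of the power calculation. That is true, so this is not a contradiction. But once baseline is in the model, the arm coefficient is the same whether the outcome is the follow-up level or the change, so adjustment does not abandon the stated outcome.

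A reader might infer several stronger points that the article does not support:

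- **Bias.** The change score is unbiased under randomisation. All hospitals are selected in the same way before allocation, so regression to the mean is expected to be equal in both arms.
- **Excess false positives.** The simulated error is in the conservative direction.
- **Serious baseline imbalance.** A 5-point imbalance at slope 0.5 would shift the change-score result by 5 × (1 − 0.5) = 2.5 points. Stratification makes that uncommon: with an assumed two-level split and a baseline SD of 11.3, it occurs in about 11% of allocations, against 32% unstratified.
- **A wholly unadjusted primary analysis.** RS-NIV is already adjusted for patient demographics and comorbidities. The gap is at hospital level.
- **Data-driven covariates in the primary result.** They are confined to the additional analyses.

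The top of the power range also needs caution. It requires equal SDs and a low correlation, neither of which the article gives. A separate simulation using raw hospital rates at the median patient count showed gains of only 1 to 6 percentage points (61 to 63%, 80 to 81%, 80 to 84% and 85 to 91%), and raw rates are not the shrunken RS-NIV endpoint.

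Finally, stratum terms may be named in an analysis plan that is not shown, so silence about them is not itself an error. The ranking of the two analyses, however, is stated in the article.

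**Conclusion.** The point holds as one of efficiency and calibration, not validity. The protocol fixes the less efficient of its two planned hospital-level analyses as primary. Relative to the stated 80%, the gain from baseline adjustment is about 2 to 13 percentage points under equal SDs (rho 0.9 to 0.3), or about 2 to 6 if selection restricts the baseline spread (slope 0.7 to 0.3). Near a slope of 1 the gain is negligible. As worded, with no stratum term, the test is also conservative, to a degree that depends on the unknown correlation and on how far bed size predicts outcome. All these figures rest on a back-solved SD of 11.3 points and assumed correlations. The direction of the preference does not depend on their exact values, and a change is worthwhile because it is cheap.

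**What to change.** Make the primary analysis the comparison of 18-month post-intervention RS-NIV between arms, adjusted for continuous baseline RS-NIV and one bed-size term. Keep the change-score ANOVA as a sensitivity analysis. Apply the same order to the sustainability comparison, which is to use similar models.

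Separately, in the additional analyses, replace covariates chosen by observed imbalance with a short list fixed before any outcome data by arm are seen. Between-arm summaries of hospital characteristics can stay as description.

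The cost is a change of wording and one or two of the 18 residual degrees of freedom. Baseline RS-NIV and number of beds are already to be collected, and neither the sample size nor the data collection changes.

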**Fig. 2 Fig2:**
[figure not shown]
Step-by-step development and evaluation of the implementation strategy. Key: NIV = Noninvasive Ventilation, COPD = Chronic Obstructive Pulmonary Disease, RT = Respiratory Therapist, TDF = Theoretical Domains Framework, ERIC = Expert Recommendations for Implementing Change, RCT = Randomized Control Trial

In step 2, we organized the specific types of determinants that influence NIV delivery using the Theoretical Domain Framework (TDF) [16]. The TDF was used as a guiding theory for this project because the desired behavior change is primarily at the individual level, e.g., convincing providers to consider NIV in any patient with severe COPD exacerbation. We summarized the barriers in the TDF domains with an eye toward choosing an implementation strategy which could overcome several of the identified barriers. Eight of the 14 domains (knowledge, skills, professional roles and identity, beliefs about capabilities, beliefs about consequences, environmental context and resources, social influences, and emotion) were present in the existing literature and our research.

Interdisciplinary teamwork, on-going education, providers buy-in, and RTs autonomy were found as the top four determinants for successful NIV delivery in COPD exacerbations. These findings suggest that to succeed, implementation strategies need to account for the complex and interdisciplinary nature of NIV therapy and the need for team coordination.

Step 3: to guide the selection of implementation strategies, we used the Expert Recommendations for Implementing Change (ERIC) [17]. The main themes that emerged from the qualitative analysis and literature review mapped to the TDF domains and the implementation strategies most likely to address those barriers are shown in Table 1. Systematic analysis of the barriers suggested that to succeed, implementation strategies for knowledge transfer need to account for the complex and interdisciplinary nature of the NIV therapy and the need for team coordination; however, these hypotheses need to be carefully tested. Interprofessional, dynamic team training for physicians, RTs, and nurses was the implementation strategy selected as targeting several key determinants [16, 18, 19].

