##### Training of the facilitators

We will organized a one day in-person training for all the NIV-COPD teams. The training will consist of 2 modules: (1) NIV knowledge and skills: delivered by NIV experts and (2) IPE: delivered by an expert in IPE and team training. The didactic training regarding NIV use in COPD will include a review of the evidence supporting the benefits of NIV, advantages of NIV as compared to invasive mechanical ventilation (IMV), selection of patients, contraindications to NIV, and management of patients while on NIV including monitoring, ventilator settings, attention to patient comfort, weaning from NIV, and decision about NIV failure and need for intubation. The didactic module will emphasize the importance of early initiation of NIV in patients with severe COPD. The second half of the training will concentrate on teaching interprofessional collaboration. Specifically, the Interprofessional Education Collaborative (IPEC) recommends four key competencies in successful IPE, which include roles and responsibilities, teams and teamwork, values and ethics, and interprofessional communication [26]. We selected the following core competencies for our interactive IPE. *Professional roles and identity:* each team member learns about abilities, tasks, duties, responsibilities, and concerns of their fellows’ team members; *values/ethics*: work with individuals of other professions to maintain a climate of mutual respect and shared values; *teams/teamwork*: apply relationship-building values and the principles of team dynamics to perform effectively in different team roles to deliver patient-center care that is safe, timely, effective, and efficient [27]. Given the demands for team coordination in NIV delivery and findings in our qualitative work, we anticipate that IPE will contribute to greater RT, physician, and nurse understanding of each other’s roles, increase team communication and functionality, and stimulate the development of shared mental models which facilitate coordination for NIV. We will use positional clarification which involves verbally presenting team members with information about their teammates’ jobs through discussion [28]. Psychological safety and speaking up will be encouraged and facilitated. For example, an RT may assume that physicians have more knowledge about NIV delivery for a particular patient than they do (because physicians are generally more knowledgeable about treatments) and remain quiet; when in fact, the RT has important information about how the patient may respond (cognitive bias) [29].

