##### Secondary outcomes

RS hospital rates of NIV failure (IMV after a trial of NIV), mortality, length of stay, and 30-day readmission among all patients with COPD.

All outcomes will be measured at the hospital level: (1) at baseline using prior 18 months of data, (2) at 18 months post-implementation to assess immediate/short term impact, and the following 18 months to assess sustainability. The 18-month assessment period is necessary to have adequate numbers of eligible COPD admissions for assessing hospital rates of NIV utilization. The time from randomization to the completion of the educational sessions with an expected duration of 3 months will not be included in the calculation of RS-NIV post-intervention. To examine penetration, we will measure providers’ exposure to educational training using participation logs.

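### Between-arm comparisons of mortality, length of stay and readmission among ventilated patients select on a post-randomisation decision that the training aims to change; all COPD admissions should be named as the comparison population

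*Protocol article*

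**What the plan says.** The protocol article's section Secondary outcomes lists NIV failure with "mortality, length of stay, and 30-day readmission among all patients with COPD". The secondary-outcome paragraph of Statistical analysis of aim 1 widens this. Hospital rates are to be calculated for NIV failure, mortality, readmission and "length of stay among ventilated patients, as well as all COPD admissions for each study period". It continues: "We will compare outcomes of OLE and IPE hospitals using models described above". The between-arm comparison therefore covers both populations, and no principal one is named.

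Three other statements bear on this:

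- Background (step 2 of the strategy's development) gives the desired behaviour change as "convincing providers to consider NIV in any patient with severe COPD exacerbation".
- Training of the facilitators says the didactic module will "emphasize the importance of early initiation of NIV in patients with severe COPD".
- Statistical analysis of aim 1 describes the risk-standardisation model as "adjusting for demographics, and comorbidities".

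The plan also says that "we assume that the patients treated in IPE hospitals will have better clinical outcomes", but in the same sentence it does not expect to detect an effect on these outcomes.

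**The concern.** Being ventilated is not a baseline characteristic here. It is a clinical decision taken after the hospital has been randomised, and the training is directed at it. If one arm ventilates a wider group of patients, the ventilated sets in the two arms are no longer comparable, and randomisation does not protect a comparison between them.

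If the added patients are at lower risk than those who would have been ventilated anyway, the ventilated group's death rate and mean stay fall although no patient does better. Demographics and comorbidities say little about how ill the patient is on arrival, so risk standardisation would not restore comparability.

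At stake is the reading of the clinical results. The plan states in advance which arm it assumes will do better. A comparison open to this artefact stands with the same status as one that is free of it.

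**Working it through.** The plan prints no mortality, length-of-stay or NIV-failure rate and no power figure for these outcomes, so there is no stated figure to reproduce. The check asks how large the artefact could be if every patient's outcome is held fixed.

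**Inputs from the protocol (Power and sample size for aim 1)**
- Median 197 eligible COPD patients per candidate hospital over 12 months.
- Median 37 ventilated patients per hospital, taken as the same 12 months.
- Candidate hospitals have a risk-standardised NIV share below 55%.
- Planned rises in NIV share: 5 points (OLE) and 20 points (IPE).

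**Assumptions**
- Baseline NIV share p = 50%; 40% to 54% as the range.
- Mortality of 10% in those ventilated anyway and 2% in everyone else.
- The whole rise comes from patients who would otherwise not be ventilated. This is the upper case.
- No death is prevented.

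**Ventilated counts.** Invasive starts stay at 37 × 0.50 = 18.5. A share of 55% needs 18.5/0.45 = 41.1 ventilated patients (4.1 added). A share of 70% needs 18.5/0.30 = 61.7 (24.7 added).

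**Mortality among ventilated patients**
- OLE: (37 × 0.10 + 4.1 × 0.02)/41.1 = 9.2%.
- IPE: (37 × 0.10 + 24.7 × 0.02)/61.7 = 6.8%.
- Spurious difference: 2.4 points.

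**Mortality among all COPD admissions, both arms:** (37 × 0.10 + 160 × 0.02)/197 = 6.9/197 = 3.5%. Difference: 0.

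**Sensitivity.** In this scenario the spurious difference reduces to (high mortality − low mortality) × 0.15/(1 − p).
- 10% and 2%, p = 45%: 0.08 × 0.15/0.55 = 2.2 points.
- 10% and 2%, p = 40% and 54%: 2.0 and 2.6 points.
- 5% and 1%, p = 40%: 0.04 × 0.15/0.60 = 1.0 point.
- 20% and 3%, p = 54%: 0.17 × 0.15/0.46 = 5.5 points.

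**Milder case.** With only 10% more patients ventilated, 10% mortality becomes (3.7 + 3.7 × 0.02)/40.7 = 9.3%.

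**Pure substitution.** If every added NIV start replaces an invasive start, the ventilated count stays at 37 with the same patients, and the artefact is zero.

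**NIV failure (denominator: NIV starts).** Assume 20% failure in the original 18.5 NIV patients.
- Newly ventilated patients failing at 5% (assumed): OLE (3.7 + 4.1 × 0.05)/22.6 = 17.3%; IPE (3.7 + 24.7 × 0.05)/43.2 = 11.4%. The rate falls with no intubation averted.
- If the added NIV starts are instead patients who would have been intubated, and they fail more often than 20%, the rate rises in IPE. The direction is open.

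**Against sampling noise** (p = 45%, 10% and 2%, 18-month periods, equal hospitals, binomial variation only). Baseline n = 37 × 1.5 = 55.5. Follow-up n = 61.1 (OLE, 9.3%) and 87.2 (IPE, 7.1%). The variance of one hospital's change is about 0.0030 in OLE and 0.0024 in IPE. With 10 hospitals per arm, SE = √[(0.0030 + 0.0024)/10] = 2.3 points, so the 2.2-point artefact is about one standard error.

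**The case against.** The case against has real weight.

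- **The sections do not conflict.** A reader might infer that the two sections define the outcomes incompatibly. They overlap: the all-admissions analysis is kept and the ventilated one is added. Had the article merely been silent on precedence, that could be left to the analysis plan. What is not mere silence is the stated between-arm comparison in a group formed after randomisation.
- **The mechanism is inferred from the training's aims.** The documents also describe substitution. Background reports lower invasive ventilation at hospitals with higher NIV rates, and the RT autonomy section pictures therapists proposing NIV in place of intubation. Under pure substitution nothing is diluted. This stands, and it makes the point conditional.
- **NIV failure.** A reader might infer that this outcome too must favour IPE. The documents do not support that, because converting patients who would have been intubated could push the rate up.
- **Little practical consequence.** The plan expects no detectable effect, the artefact is about one standard error even in the upper case, and the shrinkage in the risk-standardised rates would reduce it further. The plan also calculates the percentage not ventilated, so a shift could be seen. This limits the severity. It does not answer the point, because low power concerns detection and not bias, and the estimates will still be reported.

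**Conclusion.** The point holds in conditional form. The plan commits to comparing arms within a group whose membership the training may alter, with adjustment that does not cover acute severity, and gives that comparison the same standing as the all-admissions one.

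The spurious mortality difference between arms is about 2.2 to 2.4 points at baseline NIV shares of 45% to 50%, and 1.0 to 5.5 points over the wider ranges tried. These are upper-case figures. They rest on assumed mortality rates, on attributing the whole planned rise to newly ventilated patients, and on crude proportions. The direction holds for mortality and length of stay whenever the added patients are at lower risk or stay less long. The size shrinks to zero as the response becomes pure substitution.

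A reader might go further and conclude that the ventilated-only results are bound to favour IPE. The documents do not establish that, since they do not say how the rise in NIV will come about. The primary outcome is outside this point. It is a change that should be made, of moderate importance.

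**What to change.** 1. State that the between-arm comparison of mortality, length of stay and 30-day readmission is among all eligible COPD admissions, as Secondary outcomes already has it.
2. Report the ventilated-only figures as descriptive, labelled as not a randomised comparison, beside the proportion ventilated in each arm and period. The plan already calculates the percentage with no assisted ventilation.
3. Keep NIV failure, state its denominator as NIV starts, and label it in the same way. The all-patients wording does not fit an outcome that requires a trial of NIV.
4. Add IMV after NIV, and any IMV, each per COPD admission, as the between-arm measures.

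This is a change of wording on the same data. The cost is that effects per admission are more diluted than effects per ventilated patient, which matters little because the plan already expects no detectable effect on the secondary outcomes.
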